## Abstract

**Background:**

Central venous catheters play an important role in patient care. Real-time ultrasound-guided subclavian central venous (SCV) cannulation may reduce the incidence of complications and the time between skin penetration and the aspiration of venous blood into the syringe. Ultrasonic diagnosis of catheter misplacement and pneumothorax related to central venous catheterization is rapid and accurate. It is unclear, however, whether ultrasound real-time guidance and examination can reduce procedure times and complication rates when compared with landmark guidance and radiographic examination for SCV catheterization.

**Methods/Design:**

The Subclavian Central Venous Catheters Guidance and Examination by UltraSound (SUBGEUS) study is an investigator-initiated single center, randomized, controlled two-arm trial. Three hundred patients undergoing SCV catheter placement will be randomized to ultrasound real-time guidance and examination or landmark guidance and radiographic examination. The primary outcome is the time between the beginning of the procedure and control of the catheter. Secondary outcomes include the times required for the six components of the total procedure, the occurrence of complications (pneumothorax, hemothorax, or misplacement), failure of the technique and occurrence of central venous catheter infections.

**Discussion:**

The SUBGEUS trial is the first randomized controlled study to investigate whether ultrasound real-time guidance and examination for SCV catheter placement reduces all procedure times and the rate of complications.

**Trial registration:**

ClinicalTrials.gov Identifier:
NCT01888094

## Background

Central venous catheters play an important role in patient care, especially in the intensive care unit (ICU). However, their use is associated with various complications, which occur more frequently when catheters are placed through routes involving the subclavian vein than through routes involving the internal jugular and femoral veins
[1,2]. Nevertheless, the subclavian vein route is associated with lower rates of infection and thrombosis and remains the route of choice in the ICU
[3,4]. Real-time ultrasound-guided central venous cannulation results in a lower technical failure rate (overall and on first attempt), faster access, and a reduction in mechanical complications, although this has been validated mainly for the internal jugular vein
[5,6]. One study reported that complications and failure rates of subclavian central venous (SCV) catheterization were lower for real-time ultrasound-assisted vein location
[7]. However, the only temporal parameter recorded was the time between penetration of the skin and aspiration of venous blood into the syringe; thus, the time required for the entire procedure has never been evaluated. Ultrasonic diagnosis of catheter misplacement and pneumothorax related to central venous catheterization was reported to be a rapid and accurate method that can be easily performed by ICU physicians
[8].

The Subclavian Central Venous Catheters Guidance and Examination by UltraSound (SUBGEUS) study aims to compare the complete time required for the procedure and the rate of complications of a global ultrasound method and a standard (landmark and radiographic) method used in the routine cannulation of the subclavian vein in patients requiring a central line.

## Methods/Design

### Objectives and design

The SUBGEUS study is an investigator-initiated, single center, randomized, controlled trial approved by the Institutional Review Board of Clermont-Ferrand, France (AU-1000, Eudra-CT 2012-A01188-35). Informed consent is obtained from each participant. The SUBGEUS study is conducted in accordance with the Declaration of Helsinki and was registered on June 25, 2013, on http://clinicaltrials.gov/ as trial NCT01888094.

### CONSORT diagram

Figure 
1 shows the CONSORT diagram of the SUBGEUS trial.

**Figure 1 F1:**
[figure not shown]
CONSORT diagram of the SUBGEUS trial.

### Study population

Investigators screen consecutive patients who are admitted to the ICU and require a central venous line. Inclusion criteria are requirement for SCV catheterization, age >18 years and informed consent from the patient or his/her next-of-kin. Exclusion criteria are patient refusal, femoral or internal jugular catheterization, and impossibility of obtaining good echogenicity.

All operators must have at least three years of experience with subclavian catheter procedures and must have completed at least five ultrasound procedures.

### Randomization

Patients eligible for inclusion are randomized 1:1 in fixed blocks of 10, without stratification, by a computerized number generator list provided by a statistician not involved in the determination of eligibility or in the assessment of outcomes. All assignments are made through a dedicated, password protected, SSL-encrypted website. Randomized patients are given a number corresponding to a «SUBGEUS Number».

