### Study protocol

Patients are randomized to a ‘real-time ultrasound guidance and examination’ method or to a ‘standard’ (landmark and radiographic) method, with study treatment beginning within one hour of randomization.

The predefined length of insertion is based on patient height and calculated as: height/10 - 2 cm for right subclavian vein sites and height/10 + 2 cm for left subclavian vein sites
[9]. Patients are placed in the Trendelenburg position. The operator will evaluate the likelihood of difficult cannulation, based on various patients factors, including obesity (body mass index >30 kg/m^2^), coagulation disorders, short neck, acute respiratory failure, agitation, and history of SCV cannulation.

Before starting the procedure, the operating physician uses maximal sterile-barrier precautions, including a mask, a cap, a sterile gown and gloves and handwashing.

The various procedure times, T0 to T5, are defined as:

T0: Start of the procedure, defined as when the physician begins skin disinfection with 2% chlorhexidine. Large sterile drapes are set. If necessary, a local anesthetic (1% lidocaine solution) is applied with a 22-gauge needle. Ultrasound guided determination of the puncture site is identified in patients randomized to the ultrasound group.

T1: Skin puncture.

T2: Return of venous blood into the syringe attached to the needle, followed by correct insertion of the guide according to Seldinger’s technique. In case of uncorrected insertion of the guide, a new site is punctured, with T2 defined as the time of return of venous blood from the new puncture, followed by correct insertion of the guide.

T3: Application of dressing after catheter insertion, purge and fixation. Lines of perfusion are positioned. Ultrasound examinations are started or the radiology technician in the radiology department is contacted. The chest radiograph device is located in the ICU.

T4: The catheter is checked for placement and complications. A chest radiograph is taken and interpreted or the patient has been assessed by ultrasound examination, depending on randomization. If there is no evidence of complications or misplacement, then T4 = T5. If there are complications or misplacement, corrections are made, including a chest tube for pneumothorax, and withdrawal or repositioning if the catheter is misplaced.

T5: End of the procedure, when the catheter is accurately inserted and controlled.

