## Trial status

The trial is ongoing and is actively enrolling patients.

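### Fixed, published blocks of 10 in one unmasked sequence let someone who tracks it deduce up to one allocation in six; varying, undisclosed block sizes would remove almost all of that

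*Protocol article*

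**What the plan says.** All references are to the protocol article.

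- **Randomization:** patients are "randomized 1:1 in fixed blocks of 10, without stratification". The list is "provided by a statistician not involved in the determination of eligibility or in the assessment of outcomes", and "All assignments are made through a dedicated, password protected, SSL-encrypted website".
- **Objectives and design:** the study is an "investigator-initiated, single center, randomized, controlled trial", so there is one list for one site. The abstract gives the size: "Three hundred patients undergoing SCV catheter placement will be randomized".
- **Study protocol:** "Patients are randomized to a ‘real-time ultrasound guidance and examination’ method or to a ‘standard’ (landmark and radiographic) method". The article does not call the trial open for investigators, but the operator performs one procedure or the other and so knows each assignment once it is made.
- **Study population:** consecutive ICU patients are screened. "Exclusion criteria are patient refusal, femoral or internal jugular catheterization, and impossibility of obtaining good echogenicity".
- **Trial status:** "The trial is ongoing and is actively enrolling patients". The block size thus became public during recruitment.

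Nothing in the article says that the block size varies or is kept from investigators.

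**The concern.** In a block of 10 with five patients per arm, the rest of the block is determined as soon as one arm has used its five places. With a single unstratified list at one site and visible treatments, the information needed for that deduction is available locally: the order of past assignments and a constant, published block size.

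Foreknowledge matters only if someone can act on it before the patient is randomized. Here there is some room. A patient for whom a femoral or jugular route is chosen is outside the trial, and so is a patient whose echogenicity is judged inadequate. Under Study protocol, operators also rate how difficult cannulation is likely to be, from features such as obesity, short neck or agitation. Such features plausibly lengthen the interval from T0 to T4, which is the primary endpoint. If expected difficulty influenced entry differently according to the arm known or guessed to come next, the arms would differ in case mix on something that drives the primary outcome.

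**Working it through.** **Inputs.** Block size 10, ratio 1:1, no strata (Randomization); one center (Objectives and design); 300 patients (abstract), hence 300/10 = 30 blocks; SD 25 min, target difference 10 min and 150 per group (Sample size estimation). The article states no predictability figure, so there is none to reproduce.

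**1. Certain allocations under the stated scheme.** For a block of 2m, the expected number of allocations made after one arm is full is 2m/(m+1). With m = 5 this is 10/6 = 1.67 per block, a share of 1/6 = 16.7%. Over 30 blocks: 30 × 1.67 = 50 of 300. Enumerating all 252 possible blocks confirms this:

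| Determined allocations in a block | Share of blocks |
|---|---|
| 1 | 55.6% |
| 2 | 27.8% |
| 3 | 11.9% |
| 4 | 4.0% |
| 5 | 0.8% |

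Every block has at least one, its last place, so 30 of the 50 are last places and about 20 come earlier.

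**2. Guessing.** An observer who always names the arm that is behind in the block, and guesses at random when the arms are level, expects m + 2^(2m−1)/C(2m, m) − 1/2 correct guesses per block. With m = 5: 5 + 512/252 − 0.5 = 6.53 of 10, or 65.3%, against 50% by chance.

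**3. Alternatives.** Simulation of 300 patients, with an observer who knows the set of block sizes and all past assignments but not the order of the sizes:

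| Scheme | Certain, of 300 | Correct guesses |
|---|---|---|
| Fixed 10 | 50 | 65.3% |
| Random from 8, 10, 12, 14 | about 2 (0.7%) | 64.6% |
| Random from 4, 6, 8 | about 7 (2.2%) | about 68% |

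Varying the size removes nearly all certain knowledge but hardly changes average guess accuracy. Adding short blocks makes guessing easier.

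**4. What it could do to the primary result (illustration only).** Assume that steering happens only at the 50 determined places and shifts mean procedure time at those places by D minutes between arms. The shift in the trial estimate is then D × 50/300 = D/6. The standard error is 25 × √(2/150) = 2.89 min. The documents give no value for D, so a range is shown, with the normal approximation and no true effect:

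| D (min) | Shift D/6 (min) | Two-sided type I error |
|---|---|---|
| 5 | 0.8 | 6% |
| 10 | 1.7 | 8.9% |
| 25 | 4.2 | 30% |

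**The case against.** **The figure of 50 is a ceiling.** It needs someone to follow every assignment, in order, with the block starts, through 30 blocks. Assignments are issued one at a time through a protected website, and the article implies several operators: it plans to model variation between them and records a switch of operator. Each may know only part of the sequence. This stands, and it is why the claim is *up to* one in six. It does not remove the exposure, because one ICU team can pool what its members know. The Statistical analysis section also mentions variation between centers. Several sites sharing one list would be harder to track, but the stated design is single center.

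**The room to act is limited.** Screening is consecutive, these patients need a line, and treatment starts within an hour of randomization. This also stands: it reduces the opportunity but leaves the choice of vein and the echogenicity judgement.

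**The analysis offers some protection.** The planned regression adjusts for clinically relevant covariates, and height, weight, coagulation tests and severity scores are recorded at baseline. Differences in measured difficulty could be seen and partly corrected. A reader might infer that no planned analysis could detect or remove such bias; the article does not support that. What adjustment cannot reach is difficulty that the operator perceived and nobody recorded.

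**The scheme is a recognised one.** Permuted blocks with central allocation and an independent list maker are ordinary practice, and 10 is a fairly large block: by the same formula, blocks of 4 give 33% certain and blocks of 6 give 25%. That is fair. The point is an avoidable weakness, not an error or contradiction in the text.

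**Conclusion.** The point holds as an exposure to selection bias. With fixed blocks of 10 in one unstratified sequence, visible arms and a block size published during recruitment, an observer who tracks the whole sequence and its block starts can deduce up to 1/6 of allocations (about 50 of 300) and guess the next arm correctly 65% of the time. The arithmetic is exact for that observer. How close any investigator comes to it is unknown, and that past allocations are visible is inferred from the interventions, not stated.

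Two stronger readings are tempting. One is that investigators in fact know one allocation in six; the article does not show that anyone follows the full sequence. The other is that the trial is biased; nothing in the article shows that entry was steered, and the shifts computed above rest on assumed values of D. The change is worth making because it is cheap and removes most of the certain knowledge. It is a recommended improvement, not a flaw that invalidates the trial.

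**What to change.** For patients not yet randomized, the independent statistician should let the block in progress run to its end and then load a new list with block sizes drawn at random, for example from 8, 10, 12 and 14. The sizes should appear in no document that investigators can see until recruitment ends. Very short blocks (4 or 6) should not be added, since they raise guess accuracy.

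This lowers certain allocations from about 50 to about 2 per 300, in proportion to the patients still to be randomized. It does not help patients already enrolled, and it leaves overall guess accuracy near 65%, so guessing the likelier arm remains possible.

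Cost: a documented amendment, because the method is approved and published; a written rule for the change-over; regeneration of the list on the existing website; and a possible imbalance of a few patients if recruitment stops inside a block.

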### Study protocol

Patients are randomized to a ‘real-time ultrasound guidance and examination’ method or to a ‘standard’ (landmark and radiographic) method, with study treatment beginning within one hour of randomization.

The predefined length of insertion is based on patient height and calculated as: height/10 - 2 cm for right subclavian vein sites and height/10 + 2 cm for left subclavian vein sites
[9]. Patients are placed in the Trendelenburg position. The operator will evaluate the likelihood of difficult cannulation, based on various patients factors, including obesity (body mass index >30 kg/m^2^), coagulation disorders, short neck, acute respiratory failure, agitation, and history of SCV cannulation.

Before starting the procedure, the operating physician uses maximal sterile-barrier precautions, including a mask, a cap, a sterile gown and gloves and handwashing.

The various procedure times, T0 to T5, are defined as:

T0: Start of the procedure, defined as when the physician begins skin disinfection with 2% chlorhexidine. Large sterile drapes are set. If necessary, a local anesthetic (1% lidocaine solution) is applied with a 22-gauge needle. Ultrasound guided determination of the puncture site is identified in patients randomized to the ultrasound group.

T1: Skin puncture.

T2: Return of venous blood into the syringe attached to the needle, followed by correct insertion of the guide according to Seldinger’s technique. In case of uncorrected insertion of the guide, a new site is punctured, with T2 defined as the time of return of venous blood from the new puncture, followed by correct insertion of the guide.

T3: Application of dressing after catheter insertion, purge and fixation. Lines of perfusion are positioned. Ultrasound examinations are started or the radiology technician in the radiology department is contacted. The chest radiograph device is located in the ICU.

T4: The catheter is checked for placement and complications. A chest radiograph is taken and interpreted or the patient has been assessed by ultrasound examination, depending on randomization. If there is no evidence of complications or misplacement, then T4 = T5. If there are complications or misplacement, corrections are made, including a chest tube for pneumothorax, and withdrawal or repositioning if the catheter is misplaced.

T5: End of the procedure, when the catheter is accurately inserted and controlled.

Complications recorded include arterial puncture, pneumothorax, hemothorax, and misplacement (contralateral subclavian or jugular route; outside the superior vena cava or the right atrium).

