### Study endpoints

The primary endpoint is the procedure time between the beginning of the procedure (T0) and when the catheter is controlled (T4).

The secondary outcomes are the procedure times (T0 to T5) of the two strategies, rates of per procedure complications (pneumothorax, hemothorax, and misplacement), failure of the technique and central venous catheter infection (catheter-related sepsis without bacteremia or catheter-related bloodstream infections). Catheter-related sepsis without bacteremia and catheter-related bloodstream infections are described below:

1. Catheter-related sepsis without bacteremia is defined according to the combination of 1) fever (body temperature ≥38.5°C) or hypothermia (body temperature ≤36.5°C), 2) catheter colonization, 3) regression of fever or hypothermia within the 48 h following catheter removal and with no change in antimicrobial therapy, or presence of pus at the catheter insertion site, and 4) no other identified sources of infection.

2. Catheter-related bloodstream infections are defined as the combination of 1) fever (body temperature ≥38.5°C) or hypothermia (body temperature ≤36.5°C), 2) one or more positive peripheral blood cultures drawn 48 h before or after catheter withdrawal, 3) isolation of the same organism (same species and same susceptibility pattern) from the colonized catheter or from the catheter insertion site, or a blood-culture differential time-to-positivity of 2 h or longer, and 4) no apparent source of bacteremia other than the catheter. In patients with positive coagulase negative staphylococci bacteremia, at least two positive cultures from separate blood samples are required.

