### Statistical analysis

Statistical analyses will be performed on ITT populations. Student’s unpaired *t*-test or the Mann-Whitney test (if appropriate) will be used for primary outcome analysis. The Shapiro-Wilk test will be used to assess normality, and the Fisher-Snedecor test to assess homoscedasticity. Analysis will be adjusted by random effects linear regression to 1) take into account adjustments for possibly confounding covariates selected according to clinical relevance (for example, history of venous central catheter procedures, failure rate of the technique) and 2) consider variations within and between centers and operators. All effect sizes will be reported with 95% confidence intervals. Other continuous variables will be analyzed identically. Categorical parameters will be compared in the randomized groups using unadjusted chi-square or Fisher’s exact test. Analyses will be adjusted using the previously described adjustment variables in a logistic regression model. If the frequency of missing data is >5%, an additional analysis will be performed using the multiple imputation method (software Stata command
[23]). All analyses will be performed using Stata statistical software, release 12 (StataCorp, College Station, TX, USA).

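### T4–T5 is zero by rule for every uncorrected patient, so the Mann-Whitney test to which the plan leads would mostly re-test the correction rate

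*Protocol article*

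**What the plan says.** All references are to the protocol article.

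- **Study protocol** defines six time points, T0 to T5. For the last two it states: "If there is no evidence of complications or misplacement, then T4 = T5". Otherwise, "If there are complications or misplacement, corrections are made, including a chest tube for pneumothorax, and withdrawal or repositioning if the catheter is misplaced". T4–T5 is thus the time spent on correction, and zero where none is needed.
- **Abstract, Methods/Design** lists among the secondary outcomes "the times required for the six components of the total procedure".
- **Study endpoints** repeats: "The secondary outcomes are the procedure times (T0 to T5) of the two strategies". Complication rates are a separate secondary outcome. The primary endpoint runs from T0 to T4.
- **Statistical analysis** names Student's unpaired t-test "or the Mann-Whitney test (if appropriate) will be used for primary outcome analysis", and adds that "The Shapiro-Wilk test will be used to assess normality". An adjusted random effects linear regression follows. For the rest: "Other continuous variables will be analyzed identically". No separate treatment is given for a time that is zero by definition in most patients.

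**The concern.** A time that is zero by rule in most patients carries two different quantities: whether a correction was needed, and how long it took. A rank test on all patients is driven by the first, because every positive value outranks every zero whatever its size. The article already covers the need for correction, closely enough, through the complication rates.

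At stake is the reading of one secondary result. The article's Discussion presents the trial as testing whether ultrasound improves every procedure time. A significant T4–T5 comparison could be taken as a quicker correction step when it largely repeats the complication result. A non-significant one could hide a large difference in correction time.

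**Working it through.** **The plan's own figure.** The sample size rests on the primary outcome: difference 10 min, SD 25 min, two-sided α 0.05, power 90%. The normal formula gives 132 per arm; the t-based calculation gives 132.3, rounded up to 133, as stated. Allowing for 10% loss, 133/0.9 = 147.8, so 148 per arm or 296 in total, against the planned 300. The figure reproduces, and T4–T5 plays no part in it.

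**Inputs for T4–T5.** From the article: 150 patients per arm, the zero rule, and the test sequence. Not in the article: correction rates and correction times by arm. All such values below are assumptions.

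**Worked example.** Landmark: 22/150 corrected, 15 min each. Ultrasound: 8/150 corrected, 45 min each.

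- Mean per patient: landmark 22 × 15/150 = 2.2 min; ultrasound 8 × 45/150 = 2.4 min. Ultrasound is longer per patient and per correction.
- Mann-Whitney U for ultrasound (pairs in which the ultrasound time is longer, plus half the ties): 8 × 150 + (142 × 128)/2 = 1200 + 9088 = 10288. The null value is 150 × 150/2 = 11250.
- Ties: 270 zeros, 22 values of 15, 8 values of 45, so Σ(t³ − t) = 19,693,860. Variance = (150 × 150/12) × [301 − 19,693,860/(300 × 299)] = 152,714; SD = 390.8.
- z = (10288 − 11250 + 0.5)/390.8 = −2.46, p = 0.014, in favour of ultrasound.
- t-test on the same data: p = 0.83.

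**Sensitivity to duration.** Raise the ultrasound correction time to 60 min: the means become 3.2 v 2.2 min, but U is still 10288 and p still 0.014. Once the ultrasound corrections exceed 15 min, their length no longer enters the test. With 15 min in both arms, U = 8 × 128 + (8 × 22)/2 + 9088 = 10200 and p = 0.007, the same to three decimals as chi-square on 8/150 v 22/150 (p = 0.007).

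**When the mean reverses.** The per-patient mean is rate × duration. The arm with fewer corrections has the longer mean only if its corrections last more than the inverse ratio of the rates. Here that ratio is 22/8 = 2.75, so the threshold is 2.75 × 15 = 41.25 min.

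**Simulation.** 150 per arm, 2000 runs per row, log-normal correction times with coefficient of variation 0.5. The first two columns give the share corrected and the mean correction time. The last column is the share of runs in which Mann-Whitney was significant for ultrasound although the observed ultrasound mean was longer.

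| Ultrasound | Landmark | True mean per patient (min) | Mann-Whitney p < 0.05 | t-test p < 0.05 | Chi-square on rate p < 0.05 | Reversed |
|---|---|---|---|---|---|---|
| 10%, 20 min | 10%, 20 min | 2.0 v 2.0 | 5% | 5% | 5% | 0% |
| 5%, 20 min | 15%, 20 min | 1.0 v 3.0 | 85% | 76% | 85% | 0% |
| 5%, 40 min | 15%, 20 min | 2.0 v 3.0 | 79% | 20% | 84% | 3% |
| 5%, 60 min | 15%, 20 min | 3.0 v 3.0 | 80% | 7% | 85% | 27% |
| 10%, 10 min | 10%, 40 min | 1.0 v 4.0 | 7% | 83% | 6% | 0% |
| 10%, 40 min | 20%, 15 min | 4.0 v 3.0 | 53% | 10% | 69% | 31% |
| 5%, 80 min | 15%, 15 min | 4.0 v 2.25 | 78% | 11% | 83% | 64% |

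In every scenario run, Shapiro-Wilk (applied to the ultrasound arm) rejected normality in at least 99% of runs, and both medians were 0 in all of them. Mann-Whitney and chi-square on the correction rate gave the same significance verdict in 84% to over 99% of runs. Tripling the ultrasound correction time (rows 2 to 4) moved the Mann-Whitney rejection rate only from 85% to 80%. A fourfold difference in duration at equal rates (row 5) was almost invisible to it.

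**The case against.** **The test does not generally point the wrong way.** A reader might infer that it does. The documents do not support this, since they give neither rates nor durations, and moderate assumptions do not show it. With 10% of landmark patients corrected in 20 min and 3% of ultrasound patients in 40 min, the means are 0.10 × 20 = 2.0 and 0.03 × 40 = 1.2 min. A Mann-Whitney result for ultrasound then has the right sign per patient, although each correction takes twice as long. Reversal needs the arm with fewer corrections to have much longer ones. It is a possibility, not an expectation. The t-test and the linear model compare mean time per patient and do not reverse it.

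**Zero is a true value.** Across all randomised patients, someone who needs no correction spends no extra time. This stands. The zeros are right for total time T0–T5, and mean extra minutes per patient is a legitimate quantity. The difficulty lies only in ranking T4–T5 on its own.

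**T4–T5 is not named as a separate endpoint.** The wording under Study endpoints could mean total time. That is fair, but the abstract speaks of components, and on the natural reading as consecutive intervals T4–T5 is one of them.

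**This belongs in the analysis plan.** Partly so: the article is condensed, and Mann-Whitney is conditional on being appropriate. But the article does more than stay silent. It prescribes the same methods for all continuous variables, and they fit this one badly.

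**The consequence is small.** This stands. The primary endpoint stops at T4, and complication rates will be reported beside any T4–T5 result.

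**Conclusion.** The point holds as a minor one. If T4–T5 is analysed as a component time, the stated methods lead to a Mann-Whitney test that mostly repeats the comparison of correction rates, says almost nothing about correction time, and comes with medians of 0 in both arms. In the assumed scenarios it missed a fourfold duration difference (7% rejection against 83% for the t-test). It can favour the arm with the longer mean only when that arm's corrections are fewer and longer by more than the ratio of the rates.

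This rests on three things: reading the components as consecutive intervals, a Shapiro-Wilk rejection leading to Mann-Whitney (implied, not spelled out), and assumed rates and durations. The primary analysis, its sample size and total time T0–T5 are untouched.

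Separately, the abstract counts six components while six time points bound only five consecutive intervals. That mismatch is editorial.

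**What to change.** In Statistical analysis, add that Mann-Whitney is not used for T4–T5 taken alone, and that this interval is reported as:

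1. the number of patients needing correction in each arm, with a risk difference and 95% confidence interval;
2. the mean difference in T4–T5 per randomised patient, with a bootstrap 95% confidence interval;
3. correction time among corrected patients, descriptively (for example median and range), since these patients are a subset formed after randomisation.

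In the worked example, item 1 would read 14.7% − 5.3% = 9.3 percentage points fewer corrections with ultrasound, item 2 would be 2.4 − 2.2 = 0.2 min longer with ultrasound, and item 3 would be 45 v 15 min. The reader then sees all three facts instead of a single p-value.

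In the abstract, reconcile the six components with the five intervals T0–T1, T1–T2, T2–T3, T3–T4 and T4–T5.

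Cost: a few sentences and no new data, as the times and complications are already collected. The trial is still enrolling, so the change can precede analysis. The downside is one p-value fewer.
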